##### Participant characteristics

Frequency measures and percentages will be reported for categorical variables (gender, education, occupational status, household income, relationship status, previous meditation experience, openness to meditation). For continuous variables (age, number of children, height, weight), mean and SD will be reported. Changes in weight will be calculated using paired t-tests. In addition, it will be investigated how demographic characteristics of the participants are associated with the collected outcomes using bivariate tests, including Pearson’s r correlations.

##### Other variables

Frequency measures and percentages will be reported for method(s) of previous quit attempts, use of alternative tobacco products and ECs, participation in other smoking cessation programs, NRT use, and EC dependence. Mean and SD will be calculated for years of smoking, motivation to quit, number of previous quit attempts, and withdrawal symptoms. To assess adherence and engagement, frequencies and percentages of current EC use, and number of days of use will be reported. Mean and SD for engagement with the app will be calculated. Further, frequencies and percentages will be reported for the subjective evaluation of the EC, side effects, and adverse events.

##### Nuumi program feature utilization

As indicators for feature utilization, we will analyze a set of variables including (1) the number of completed behavioral therapy lessons, (2) the number of meditation audios completed and/or repeated, (3) the number of toolbox exercises completed and/or repeated, (4) the number of times the progress tracking feature was accessed, and (5) the number of days the nuumi EC was used. A total engagement score will be calculated across all intervention components. For each of the five utilization variables, a median split will be conducted, each resulting in two categories of 0 (“below median utilization”) and 1 (“above median utilization”). The five scores will be added, resulting in a single score (ranging from 0 to 5). Two logistic regressions will be performed with total program engagement as the predictor variables and 7-day PPA from smoking at 4-weeks and 8-weeks post-baseline as the dependent variables (with 0 indicating “non-abstinent” and 1 indicating “abstinent”). To examine the relationship between feature utilization and smoking cessation, a total of 10 univariate logistic regressions for each of the five features will be performed to predict 7-day PPA from smoking at 4-weeks and 8-weeks post-baseline. The predictor variable will be the respective app feature utilization, and 7-day PPA will be the dependent variable.

To control for confounding effects on the relationship between feature utilization and smoking cessation outcomes, we will control for baseline characteristics that significantly differed by smoking status at t_1_, or t_2_, or both. To identify these variables, independent samples t-tests will be conducted for continuous variables, and chi-square tests for categorical variables.

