##### Nuumi program feature utilization

In addition to the self-reported EC and app utilization data, app feature utilization data of the nuumi program will be collected by the manufacturer of nuumi, Sanos Group GmbH, for the first 8 weeks after program initiation. Using this data, separate secondary analyses will be conducted to investigate the degree to which users engaged with the individual program features, and the relationships between utilization of individual features and smoking abstinence at 4 weeks and 8 weeks post-baseline. Utilization metrics collected by Sanos Group GmbH will include (1) the number of behavioral therapy lessons completed, (2) the number of meditations completed and/or repeated, (3) the number of toolbox exercises completed, (4) the number of times the progress tracking feature was accessed, and (5) the number of days the EC was used.

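### The total engagement score adds five median-split counts, which loses some power in a sample of about 70 and does not guarantee the stated 0–5 range

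*Protocol article*

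**What the plan says.** The rule stands in the Protocol article, Statistical methods, *Nuumi program feature utilization*. Five utilization variables are listed, among them "the number of toolbox exercises completed and/or repeated" and "the number of days the nuumi EC was used". The text continues: "For each of the five utilization variables, a median split will be conducted". It defines the two codes in these words: "each resulting in two categories of 0 (“below median utilization”) and 1 (“above median utilization". Then: "The five scores will be added, resulting in a single score (ranging from 0 to 5").

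The score has one stated inferential use: "Two logistic regressions will be performed with total program engagement as the predictor variables", with 7-day abstinence at weeks 4 and 8 as the outcomes.

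Ten further regressions take the features one at a time: "The predictor variable will be the respective app feature utilization, and 7-day PPA will be the dependent variable". The text does not say whether that predictor is the count or the split code.

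The section of the same name under Outcomes says the manufacturer collects the data "for the first 8 weeks after program initiation" and describes these as separate secondary analyses.

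**The concern.** All five variables are integer counts, and several have a natural floor or ceiling. A median split gives someone just above the median the same code as the heaviest user, so most of the ordering within each half is lost before the five codes are added.

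The split also behaves poorly when values pile up. If half the sample or more shares the lowest or highest possible value, that value is the median, and one of the two categories may be empty. The component then contributes the same number for everyone, and the score has fewer levels than the text states.

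At stake is the power and interpretability of two exploratory regressions in a sample of about 70. The primary outcome does not depend on the score.

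**Working it through.** **Inputs from the protocol.** Target sample 70 (*Sample size*). Five counts, each coded 0 or 1 and summed. Eight-week window, so 8 × 7 = 56 possible days of e-cigarette use. Alpha 0.05 two-sided, which is stated for the paired t-tests and assumed here for the regressions.

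**Inputs assumed.** The abstinence rate, effect size, correlations and count distributions are not in the protocol.

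**Step 1: the stated range.** Five 0/1 codes sum to a minimum of 5 × 0 = 0 and a maximum of 5 × 1 = 5. The stated range is reproduced, provided every component takes both values.

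**Step 2: when a component becomes constant.** With n = 70 the median averages the 35th and 36th ordered values. It equals the floor when at least 36 people are at the floor, and the ceiling when at least 36 are at the ceiling. If each person is there with probability p, the chance is P(Binomial(70, p) ≥ 36). For p = 0.55 the mean is 38.5 and the SD is √(70 × 0.55 × 0.45) = 4.16, so the normal approximation gives Φ((38.5 − 35.5)/4.16) = Φ(0.72) ≈ 0.76. Simulation gave:

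| Share at floor or ceiling | Toolbox at zero, ties coded 1: constant | E-cigarette on all 56 days, ties coded 0: constant |
|---|---|---|
| 40% | 3% | 4% |
| 50% | 47% | 46% |
| 55% | 76% | 77% |
| 60% | 94% | 94% |

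Under the opposite tie rule each of these items was never constant. Coding ties as 1 fails at the floor and coding ties as 0 fails at the ceiling, so no single rule applied to all five variables protects against both. One constant item changes the range to 1–5 (constant 1) or 0–4 (constant 0).

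**Step 3: power of the composite, normal components.** N = 70, 40% abstinent, correlation between components 0.2 to 0.5, and the point-biserial test as a proxy for the logistic slope:

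| Odds ratio per SD | Sum of continuous components | Sum of split codes |
|---|---|---|
| 1.5 | 36–37% | 28–32% |
| 2.0 | 75–76% | 64–66% |
| 2.5 | 92–93% | 83–87% |

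At matched correlations the loss is about 5 to 12 points.

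**Step 4: power of the composite, skewed counts.** The counts were Poisson with lognormal means, log-scale SD 1 to 2, correlation 0.2 to 0.6, and ties coded 0. The intercept was −0.45, so abstinence at average engagement is 1/(1 + e^0.45) = 0.39. The slope was 0.7, an odds ratio of e^0.7 = 2.01 per SD.

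- Averaged percentile ranks, or averaged standardized log(1 + count), beat the split score by about 5 to 13 points in every scenario.
- Averaged raw z-scores did not. At log-SD 2 they had 49–52% power against 62–68% for the split. Their lead at log-SD 1 was only a few points.

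**The case against.** The strongest defence is that this is a secondary analysis in a study the protocol calls exploratory and mainly descriptive. No decision rule or power claim rests on the score, and a 0–5 count is easy to read. That stands, and it limits the weight of the point.

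The constant component is also conditional. The documents give no usage distribution, and the device is ordered by voucher and posted, so daily use by half the sample is not a given. That stands too: the range is not guaranteed, but the protocol gives no basis for saying it will fail.

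Three stronger readings are tempting and are not supported.

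- A reader might apply the textbook loss for one split normal predictor (2/π = 64% of the information, so 70 × 0.637 ≈ 45 participants). The split is stated only for the composite, which loses less. The single-feature models may use the counts themselves.
- A reader might infer that the score cannot be carried into the later randomized trial. A pilot median can be reused as a fixed cut, and ranks or z-scores depend on the sample just as much. The Discussion foresees single-feature analyses and a different progress score, not this one.
- A reader might treat the strict labels as leaving people at the median uncoded. The text says each split yields two categories, so everyone is presumably assigned. The side on which ties fall is detail an article can leave to the full protocol or analysis plan.

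The defence does not justify the split itself. It is a stated choice, and a better predictor is available from the same data.

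**Conclusion.** The point holds, with modest impact. The split-and-add construction costs roughly 5 to 13 power points in the two total-engagement regressions compared with a rank- or log-based score. The figure rests on N = 70, about 40% abstinent, a log odds ratio of 0.7 per SD and skewed counts. All of these except N are assumptions, and with fewer analysable participants absolute power would be lower. The 0–5 range depends on no variable having about half the sample at its floor or ceiling with the unfavourable tie rule. The ten single-feature regressions, as written, are not shown to be affected, and the primary outcome is untouched.

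**What to change.** In the two total-engagement logistic regressions, replace the 0–5 score with the mean of the five components after percentile-ranking each count, using mid-ranks for ties. Standardizing log(1 + count) and averaging is an acceptable alternative. Report the odds ratio per 1 SD of this mean. Do not use z-scores of the raw counts, which can do worse than the split when counts are strongly skewed. A ranked or log-transformed component is constant only if every participant has the same value, so the floor and ceiling problem largely disappears.

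The 0–5 score can still be shown descriptively. The cost is a change of analysis wording, with no new data. The drawback is that the score is slightly harder to explain than a count from 0 to 5.

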### Statistical methods

#### Quantitative data analyses

Analyses will be conducted using the statistical software R, version 4.4.0 (R Core Team, 2024). Given the exploratory nature of this study, data analyses will primarily be descriptive. For categorical variables, frequencies and percentages will be reported. For continuous variables, mean and standard deviation (SD) will be reported. If applicable, statistical comparisons for paired data will be applied to compare scores observed before and after program participation. Statistical significance will be evaluated using a repeated measures two-tailed t-test; the alpha level will be set at 0.05 and a 95% confidence interval will be used. Intention-to-treat (ITT) analyses will be conducted, assuming all individuals not completing a follow-up survey have resumed smoking. In addition, complete cases will be analyzed, i.e. only participants completing the t_3_ and t_4_ survey, respectively, will be included in these analyses. Percentages and patterns of missing data will be assessed using Little’s Missing Completely At Random test and adequate data imputation techniques will be used, if applicable.

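### The engagement-abstinence models do not stop utilization before the outcome, and missing-equals-smoking may add to the association: moderate, secondary analyses only

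*Protocol article*

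**What the plan says.** **Utilization window.** Under Outcomes (Nuumi program feature utilization), the manufacturer collects five usage metrics "for the first 8 weeks after program initiation". The stated aim is to study "the relationships between utilization of individual features and smoking abstinence at 4 weeks and 8 weeks post-baseline".

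**Predictor and models.** Under Statistical methods (same subheading), each metric is split at its median into 0 or 1. "The five scores will be added, resulting in a single score (ranging from 0 to 5"). Two total-score models follow: "Two logistic regressions will be performed with total program engagement as the predictor variables and 7-day PPA from smoking at 4-weeks and 8-weeks post-baseline". For the single features, "a total of 10 univariate logistic regressions for each of the five features will be performed"; the sensible reading is 5 features x 2 time points = 10 models in all. No utilization count ending at week 4 is mentioned.

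**Adjustment.** "we will control for baseline characteristics that significantly differed by smoking status at t_1_, or t_2_, or both". Only baseline variables can enter.

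**Missing outcomes.** Under Quantitative data analyses, the intention-to-treat rule is "assuming all individuals not completing a follow-up survey have resumed smoking", with no restriction by time point. The complete-case alternative is restricted: "only participants completing the t_3_ and t_4_ survey, respectively, will be included in these analyses". The same paragraph also allows suitable imputation where applicable, without tying it to a time point. The utilization section does not say which of these rules its regressions follow.

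**The concern.** There are two separate routes to an association that does not reflect engagement helping people quit.

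1. **Timing.** If utilization logged after week 4 enters the model for week-4 abstinence, the outcome can drive the predictor. The e-cigarette is meant to replace cigarettes, and participants may stop using it or the whole program. Someone who has gone back to smoking may therefore log fewer e-cigarette days and fewer lessons in weeks 5 to 8. Adjusting for baseline characteristics cannot remove an effect that arises after baseline.
2. **Coding.** If people who skip the survey also use the program less, counting them as smokers puts low use and the smoking label in the same people.

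Both routes push toward finding that engagement goes with abstinence. The article says that the pilot should inform a later RCT and that app-behavior data will be used to refine the product with the manufacturer, so a misleading feature-level result could carry forward.

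**Working it through.** The article states no error rate, power or effect size for these models, so there is no figure of the plan's own to reproduce.

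**Step 1. Where the logging window lies relative to each outcome.** The window is 8 x 7 = 56 days. Take program start and baseline as the same day, with surveys answered on schedule.

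| Model | Before the 7-day window | Within it | After the outcome |
|---|---|---|---|
| Week 4 (outcome days 21 to 28) | 21/56 = 37.5% | 7/56 = 12.5% | 28/56 = 50% |
| Week 8 (outcome days 49 to 56) | 49/56 = 87.5% | 7/56 = 12.5% | 0% |

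These are shares of calendar time, not of use. A survey answered at the end of the permitted two weeks lowers the week-4 share after the outcome to (56 - 42)/56 = 25%. A program start later than baseline raises it. The week-4 problem touches 1 of 2 total-score models and 5 of 10 feature models.

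**Step 2. Simulation setup.** From the article: N = 70, five usage variables each split at the median, a 0 to 5 score, logistic regression, alpha 0.05. Assumed: two-sided Wald test and 40% true abstinence, independent of engagement in weeks 1 to 4. For each person:

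- E1 = standard normal - gap x (non-responder)
- E2 = 0.7 x E1 + sqrt(0.51) x noise + shift x (abstinent at week 4)
- L = (E1 + E2)/2, standardized
- each usage variable = sqrt(0.5) x L + sqrt(0.5) x noise

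There were 2,000 runs per scenario. The Monte Carlo standard error is sqrt(0.05 x 0.95/2000) = 0.5 percentage points near 5%.

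**Step 3. Timing alone** (full response, 8-week totals against week-4 abstinence).

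| Extra use by abstainers in weeks 5 to 8 | False positives | Median OR per score point |
|---|---|---|
| 0 SD | 5.3% | 1.00 |
| 0.5 SD | 14.3% | 1.14 |
| 1 SD | 40.6% | 1.30 |
| 1.5 SD | 75.5% | 1.50 |

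**Step 4. Coding alone** (shift = 0, non-responders counted as smokers). Entries are false positives.

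| Non-response | Gap 0 | Gap 1 SD | Gap 1.5 SD |
|---|---|---|---|
| 10% | 3.7% | 6.9% | 8.7% |
| 20% | 4.9% | 11.0% | 19.1% |
| 30% | 4.9% | 17.9% | 32.7% |
| 40% | 4.3% | 23.8% | 44.9% |

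Analyzing respondents only, with no shift, gives 3.5% to 5.0% throughout, with odds ratios of 0.99 to 1.01. That result depends on the simulation making non-response unrelated to true abstinence.

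**Step 5. Both together.** With 20% non-response, a 1 SD gap and a 0.5 SD shift, false positives are 31.4%. With 30%, 1 SD and 1 SD they are 64.6%.

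**Step 6. Hand check of the coding route, at its extreme.** Take 50 responders, half abstinent with no association, and 20 non-responders all below the median. Above the median: 17.5 abstinent, 17.5 not. Below: 7.5 abstinent, 7.5 + 20 = 27.5 not.

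- OR = (17.5 x 27.5)/(17.5 x 7.5) = 3.67
- SE of log OR = sqrt(1/17.5 + 1/17.5 + 1/7.5 + 1/27.5) = 0.533
- z = 1.299/0.533 = 2.44, p = 0.015

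**The case against.** The strongest reply is that the article gives a collection window and never says that full 8-week totals enter the week-4 models. The single score may only mean that five splits are added into one number, and an extraction cut-off is detail that a full protocol or SAP could hold. That stands in part: use of the full totals is an inference. It is still the most direct reading, because the article sets out score construction, model count and covariate selection in detail and describes one score for both outcomes.

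A reader might infer more than the text supports:

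- **That all twelve models use post-outcome data.** Only six can do so to any real extent. At week 8 the problem is mainly overlap. A late program start could push logging past the outcome, but a late survey answer works the other way.
- **That missing-equals-smoking is the only rule reaching t1 and t2.** Imputation is also allowed without a time limit, and the utilization section names no rule.
- **That bias is built in.** The coding route needs non-responders to be less engaged, and the article gives no attrition or usage figures. With equal engagement the error rate is nominal.
- **That the plan makes a causal claim.** The stated aim is relationships and the study is called exploratory, although the analysis section speaks of prediction and of controlling confounding. If relapsed users disengage, the association is real but does not show that engagement helped.

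It is also fair to say that an earlier cut-off does not end reverse causation. Someone who relapses on day 10 may use the program less from then to day 21 and still be smoking at week 4.

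**Conclusion.** The point holds as a moderate one. As most directly read, the week-4 models let in utilization logged after the outcome, about half of the window when everything runs on schedule, and the week-8 models overlap the outcome window. Baseline adjustment does not help. The general missing-equals-smoking rule can add to the same association at t1 and t2, where no complete-case check is planned.

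Under the assumed gaps, false positives rise from about 5% to 14% to 41% for timing (0.5 to 1 SD shift) and to 11% to 18% for coding (20% to 30% non-response, 1 SD gap). The direction follows from the mechanism whenever abstainers use the program more after the outcome or non-responders use it less. The size rests on assumed attrition, use gaps and 40% abstinence. The odds ratio of 3.67 is an extreme case and not an expected value.

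This does not call the trial's efficacy results into question. These are separate secondary analyses in an exploratory pilot, and the 7-day abstinence rates at t3 and t4 do not depend on them.

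**What to change.** 1. **Separate predictors for each outcome.** Build utilization variables from the dated logs, counted from baseline and stopped before that participant's 7-day outcome window: about day 21 for week 4 and day 49 for week 8, moved later if the survey is answered late, within the 8 weeks logged. Recompute the median splits and the 0 to 5 score for each window.
2. **Missing outcomes.** State the rule for these models. Extend the complete-case analysis, or an imputation analysis, to t1 and t2 and report it beside missing-equals-smoking. Neither is guaranteed unbiased, so a disagreement between them is itself informative.
3. **Interpretation.** Describe the results as associations and note that early relapse can still lower use inside the shortened window.

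**Cost.** A wording change and a dated extraction of data already being collected. The app displays daily puffs, but that all five metrics carry dates is an assumption to confirm with the manufacturer. Exposure windows become somewhat shorter and the respondent analysis has fewer participants. Moving the cut-off for late surveys gives unequal exposure lengths, which use per day would handle. Making the respondent analysis the main one, or adding models for t3 and t4, is a matter of judgment and is not needed to meet this point.

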##### Sample size

Formal sample size calculations are not required for single-arm pilot studies [73]. Target sample size estimation is based on single-arm pilot studies evaluating interventions for smoking cessation [74–76]. In order to address the primary and secondary aims of this trial, and to account for attrition, the target sample size is 70 participants.

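### Adjustment covariates for the feature-utilization models are chosen by significance against smoking status in about 70 people, a screen that does not reliably control confounding

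*Protocol article*

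**What the plan says.** All references are to the protocol article. Under Statistical methods, Nuumi program feature utilization, two logistic regressions relate a total engagement score to 7-day abstinence at weeks 4 and 8. In addition, "a total of 10 univariate logistic regressions for each of the five features will be performed". I read this as five features at two time points, so ten single-feature models and twelve models in all.

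The next paragraph gives the purpose of adjustment, "To control for confounding effects on the relationship between feature utilization and smoking cessation outcomes", and the rule, "we will control for baseline characteristics that significantly differed by smoking status at t_1_, or t_2_, or both". The variables are to be found as follows: "independent samples t-tests will be conducted for continuous variables, and chi-square tests for categorical variables".

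Under Quantitative data analyses, "the alpha level will be set at 0.05"; no separate threshold is given for the screen. Non-responders are handled by "assuming all individuals not completing a follow-up survey have resumed smoking". Under Sample size, "the target sample size is 70 participants", with no power calculation behind it.

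**The concern.** A confounder of the link between feature use and abstinence must be related to both. The rule tests only one of these relations. A variable strongly tied to utilization and moderately tied to smoking status can fail the test and go unadjusted. A variable unrelated to either can pass by chance and use up a model term. In a sample this small, a non-significant difference is weak evidence that a variable is unimportant.

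The covariate set also depends on the same outcome data that the models then analyse, and ordinary confidence intervals ignore that step. At stake are the adjusted odds ratios for individual app features. These could feed into the refinement of the intervention and the later RCT, both of which the article describes.

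**Working it through.** **The plan's own figure.** None exists. The article gives no miss rate, effect size or expected abstinence rate.

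**Inputs from the article.** N = 70; alpha 0.05; t-test or chi-square screen; a variable is kept if it is significant at week 4, week 8 or both.

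**Assumptions not in the article.** The screen uses two-sided 0.05. Missing responses count as smoking, so N stays at 70. Abstinence is 30% or 40% at each time point. The latent correlation of abstinence between the two time points is 0.6 or 0.8. The true SMD by smoking status is 0.3 to 0.5.

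**Step 1: one test at one time point.** Power comes from the noncentral t with df = 68 and noncentrality d x sqrt(n1 x n2 / N).
- 28 v 42, d = 0.5: 0.5 x sqrt(16.8) = 2.05; power 0.524, missed 48%.
- 21 v 49, d = 0.5: 0.5 x sqrt(14.7) = 1.92; power 0.472, missed 53%.
- 28 v 42, d = 0.3: power 0.228, missed 77%.

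**Step 2: the stated rule, either time point.** Two tests give two chances of entry, so step 1 overstates the miss rate. I simulated latent normals L1 and L2 with correlation rho, calling a participant abstinent at a time point when L exceeds the cut-off for the assumed share. The covariate is X = b(L1 + L2)/sqrt(2 + 2 rho) + sqrt(1 - b^2) Z, with b set to give the required SMD. X is kept if either t-test has p < 0.05. Results from 40,000 runs per setting:

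| Abstinent | rho | Missed, SMD 0.5 | Missed, SMD 0.4 | Missed, SMD 0.3 | Null variable enters |
|---|---|---|---|---|---|
| 30% | 0.6 | 34.7% | 50.6% | 66.6% | 0.094 |
| 30% | 0.8 | 38.2% | 54.2% | 69.0% | 0.090 |
| 40% | 0.6 | 30.1% | 46.6% | 63.8% | 0.095 |
| 40% | 0.8 | 32.9% | 49.6% | 66.1% | 0.088 |

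Allowing a point or two for simulation and calibration, the miss rates are 30-38%, 47-55% and 63-71%. Null entry, allowing likewise, is 0.085 to 0.10.

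**Step 3: at least one false entry.** The formula is 1 - (1 - a)^k for k independent null candidates.
- k = 10: 1 - 0.915^10 = 0.59 to 1 - 0.90^10 = 0.65.
- k = 20: 1 - 0.915^20 = 0.83 to 1 - 0.90^20 = 0.88.
- Expected false entries at k = 20: 20 x 0.085 = 1.7 to 20 x 0.10 = 2.0.

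The range for k is an assumption. The Participant characteristics paragraph lists 11 variables, and Table 2 adds others measured at baseline, such as cigarettes per day (CPD), urges, stress, mindfulness, self-efficacy, dependence and withdrawal.

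**Step 4: room for covariates.** At 40% abstinence there are 0.40 x 70 = 28 events; at 30%, 21. At the conventional 10 events per term (a rule of thumb, not in the article), 28/10 = 2.8 and 21/10 = 2.1 terms. One term is the feature itself, which leaves 1.8 or 1.1 for covariates.

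**The case against.** The strongest reply is about weight. The article calls these separate secondary analyses in an exploratory, mainly descriptive study. They use week 4 and week 8 outcomes, and the limitations section leaves the question of which features matter to the later RCT. This stands, and it limits the importance of the point. It does not rescue a rule that fails its own stated purpose. Nor would a fuller plan remove the difficulty, because the rule is written out here. The candidate list and any cap on covariates may well be in that fuller plan, so I do not count their absence.

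Several stronger readings are tempting and should be resisted:
- A reader might infer that real confounders are missed about half the time. That is the rate for a single test at an SMD near 0.5. Under the stated rule it is nearer one third at 0.5, about half at 0.4 and about two thirds at 0.3.
- A reader might equate a missed variable with a missed confounder. The calculation fixes only the difference by smoking status and no relation to utilization, so it does not measure bias in any odds ratio.
- A reader might fault the rule for carrying a week-8 covariate into the week-4 model. Sharing one set across time points is reasonable, and the fix does the same.
- A reader might see a contradiction in models called univariate and then adjusted. The text can be read as one feature at a time, then adjusted. That is mainly a labelling matter.

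**Conclusion.** The concern holds for the secondary feature-utilization models. Selecting covariates only by significance against smoking status does not reliably control confounding of the utilization-abstinence association. It leaves out variables that truly differ by outcome in roughly 30% to 71% of cases for SMDs from 0.5 down to 0.3, and it probably admits at least one unrelated variable (59-88% with 10-20 independent null candidates).

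These sizes depend on the listed assumptions. Correlated candidates would lower the chance of at least one false entry, though not the expected number. Analysing complete cases would raise the miss rates. If each time point kept its own covariate set, the single-test rates in step 1 would apply instead. The criticism that utilization is ignored depends on none of these figures. The primary outcome, reported as a number and percentage abstinent at weeks 12 and 24, is untouched.

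**What to change.** Remove the significance screen. Name one or two covariates now on subject-matter grounds, from those Table 2 schedules at t_0_: for example, baseline CPD or nicotine dependence, and baseline self-efficacy. Use the same set in all 12 models. Fit them by Firth-penalized logistic regression, because events may be few: two covariates plus the feature make three terms, which is 28/3 = 9.3 events per term at 40% abstinence and 21/3 = 7 at 30%. Report the unadjusted odds ratio beside each adjusted one. Replace the univariate label with single-feature models, unadjusted and adjusted.

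The cost is a change of analysis wording, with no new data. The downside is that a chance imbalance in a variable not on the list stays unadjusted; that should be stated as a limitation.
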